Our proposal will address some of the limitations in the current evidence base which were identified in the Cochrane review. The review stated that large effectiveness studies are needed. The review stated that “few studies include follow-up after six months”. The review stated that previous work has often excluded large numbers of potential participants. The review also recommended that future work should examine mediators and moderators of adherence, should examine differences between responders and non-responders, and should pay systematic attention to any safety issues which have rarely if ever been examined in previous work. We will address all these issues in our proposal. Our methodology is also informed by our previous work. In a previous study using the CCBT intervention MoodGYM which was developed by the same ANU team as E-Couch, the applicants (led by [name]) showed that they could recruit 3070 participants to a randomized controlled trial in a period of two weeks using advertisements on the NHS Choices website (www.nhs.uk) [[name] et al., 2013]. Participants were invited to participate in a ‘mental fitness’ intervention and were allocated to MoodGYM or waiting list control condition. The study showed that relative to control, MoodGYM was effective at increasing mental wellbeing scores, and reducing depression and anxiety scores among a general population of internet users of a health website. A major lesson from this study was that internet trial recruitment tends to be “easy in, easy out” with high levels of attrition. The current proposal will therefore incorporate a number of low cost measures that have previously been shown to combat attrition in internet studies including the use of automated text (SMS) messages.

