In addition to the SPIN and SOPHS, eligible participants will be required to complete a battery of self-report baseline questionnaires, and in line with all other trial procedures these will be collected online through the trial portal. These questionnaires will collect demographic characteristics (age, sex, education, employment, marital status etc.), and we will measure social anxiety symptoms (SPIN and SOPHS as above, and Brief Fear of Negative Evaluation BFNE-S scale), depression (CES-D), mental wellbeing (SWEMWBS), quality of life (SF-36), and current use of health services and psychological interventions (including self-help).

Once baseline measures are completed, eligible participants will be randomized in a 1:1 ratio with no stratification, using computer generated random number sequence run through an automatic online programme. Participants in the intervention arm will be given access to a password-protected website and will be encouraged to access and use the self-guided intervention over a period of up to 6 weeks (although they can work through the intervention at their own pace). They will receive one text message within 24 hours of randomisation to thank them for participating and to remind them to access the intervention, and one further text message towards the end of the 6 week period to thank them again and to remind them that they will shortly be asked to complete follow-up measures. They will also receive three email reminders during the six-week period (both intervention and control will receive the reminders – at 1 week, 3 weeks, and 5 weeks). Participants in the Control arm will receive the same reminders and will be given access to the intervention after final follow-up (12 months). Participants in the intervention arm will be offered continued access to the intervention once the trial is completed.

*Follow-up measures*

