Self-report follow-up measures of social anxiety symptoms (SPIN, SOPHS, and Brief Fear of Negative Evaluation BFNE-S scales), depression (CES-D), mental wellbeing (SWEMWBS), quality of life (SF-36), and current use of health services and psychological interventions, and time off from work or study due to psychological problems will be taken at 6 weeks (following completion of the self-guided intervention), 3 months, 6 months, and 12 months. At each follow-up point they will receive notification of follow-up measures by email and by text message, and if measures are not completed they will receive up to three follow-up emails.

We will also record usage data (total number of logins, total page views, time on site). We will record measures of adherence to the intervention (number of components of E-Couch completed) and attrition from the trial (loss-to-follow-up at each time point). We will also record any safety (adverse) events (captured through monitoring participant feedback, and through questions at each follow-up period). We do not anticipate adverse events in a trial of a low intensity online self-help tool for a subclinical population. However our adverse event monitoring will include assessment of feedback from participants (including routine questions asked at each follow-up period as well as ad hoc correspondence such as emails or telephone calls) to see if these report an issue such as distress or anxiety caused by the intervention. In the first instance any possible adverse event will be reviewed by the study team (trial manager in discussion with lead investigator), and immediate action taken (such as withdrawing a participant who reports distress). If the event is classified as an adverse event it will be referred to the Trial Steering Committee (with independent chair) who will also have the role of Data Monitoring Committee for their consideration.

*Primary outcome measure*

This will be the change in self-reported social anxiety score using the 17-item SPIN. This measure has been shown to have adequate internal consistency, test-retest reliability, construct validity and sensitivity to change following intervention [Letamendi et al., 2009].

*Secondary outcome measures*

These will include social anxiety measured using the FNE scale; depression (CES-D); mental wellbeing (SWEMWBS); quality of life (SF-36); and safety events.

*Statistical methods*

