The primary statistical analysis will be carried out on the basis of intention-to-treat (ITT). We will endeavour to obtain full follow-up data on every participant to allow full ITT analysis, but we will inevitably experience the problem of missing data due to withdrawal, loss to follow up, or nonresponse to some questionnaire items. The results from the trial will be prepared as comparative summary statistics with 95% confidence intervals. All the tests will be done at a 5% two-sided significance level. The study results will be reported in accordance with the CONSORT (Consolidated Standards of Reporting Trials) 2010 statements. A full statistical analysis plan will be prepared before the recruitment starts.

To understand participant disposition, a flowchart showing numbers of participants screened, randomised and those who are available for the final analysis populations will be constructed. Reasons for withdrawal, exclusions or losses to follow-up will be shown at each stage during the study by intervention group.

A mixed effects model will be used to analyse the primary outcome (SPIN score), utilising data collected at 6 weeks, 3, 6 and 12 months from randomisation. An interaction between time and randomised group will be fitted to allow estimation of treatment effect at each time point. The model will adjust for the SPIN score at baseline gender.

Analysis of secondary outcomes, such as scores to measure social anxiety (FNE scale), depression (CES-D), mental wellbeing (SWEMWBS), and quality of life (SF36) will be similar to the method used for the primary outcome. Safety data will be analysed using Fisher’s exact or Chi-squared tests. Other binary outcomes will be analysed using generalised linear model with log link function.

For both primary and secondary outcomes we will include subgroup analyses of baseline factors which may influence the intervention effect (moderators). Baseline subgroups will be compared by including interaction terms in the model (baseline subgroup by treatment group interaction). Baseline factors to be compared include: age; gender; educational level; baseline level of sub-clinical social anxiety symptoms

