We will do sensitivity analysis for the primary outcome using methods which do not assume a MAR mechanism such as pattern-mixture models, to assess the robustness of this assumption. If different results are obtained from a pattern-mixture model compared to the mixed effects model then it is likely that the MAR assumption is not valid. As part of our exploration of treatment effects we will also produce a per-protocol or completer analysis with appropriate caveats.

*Sample size*

Although, previous studies and the recent systematic review have suggested a large treatment effect observed with supported internet-delivered interventions, we believe this treatment effect is too optimistic for a self-guided treatment, especially in a sub-clinical population group, and is also likely to be smaller in pragmatic settings. For this reason, we intend to recruit 2104 participants (i.e. 1052 per group) to this trial, which will provide 90% power to detect a small between group effect size of Cohen's d=0.2 at 5% two-sided significant level. A small effect like this may not be that important to the individual but is potentially important in population terms, in a public health intervention. This sample size has also accounted for a high level of potential attrition of up to 50% (obviously we will aim to mitigate this through frequent email and text message reminders but we need to be realistic about self-guided internet interventions and the likely level of attrition). We believe this is entirely feasible and achievable using our previous recruitment strategy and given the high population prevalence of social anxiety symptoms.

*Economic evaluation*

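### After the first notice at each follow-up, non-completers are chased by email only and no SPIN-only fallback is stated, although the protocol relies on text messages against attrition of up to 50%

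*Protocol*

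**What the plan says.** Section 10 of the Protocol, under Follow-up measures, sets visits at 6 weeks and 3, 6 and 12 months. Each opens with a notice by email and text. For people who do not respond the rule is: "if measures are not completed they will receive up to three follow-up emails". The measures are SPIN, SOPHS, BFNE-S, CES-D, SWEMWBS, SF-36, service use, and time off work or study, with safety questions at each visit.

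Text messages are given a definite role elsewhere. Section 9, under Our approach, draws on an earlier internet trial with high attrition and promises "low cost measures that have previously been shown to combat attrition in internet studies including the use of automated text (SMS) messages". Section 10, under Sample size, allows for loss of up to half the participants and says "we will aim to mitigate this through frequent email and text message reminders". Under Eligibility screening and consent, a working mobile number is required for text reminders, and consent covers contact by email and text. Under Initial trial flow, both arms get one text within a day of randomisation and one near week 6.

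The only telephone contact planned for non-completers (end of the Qualitative study section) is up to 10 interviews in the intervention arm about reasons for loss. They do not collect outcomes.

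**The concern.** The channel that the protocol justifies, requires at entry and obtains consent for is not used again once a person has failed to answer the first notice, which is when attrition is actually happening. Nor is there a short route for someone who will not face the whole battery but might answer the one scale on which the trial is judged. SPIN has 17 items. SPIN, BFNE-S (8) and SF-36 (36, from its name) already make 17 + 8 + 36 = 61, before SOPHS, CES-D, SWEMWBS, service use, time off and safety.

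The primary analysis is by intention to treat, with a mixed model valid under missing at random. People who abandon the tool, or tire of a 12-month wait, may differ from responders in ways that observed data do not capture, and differently in each arm. The planned regression of non-response on baseline variables cannot exclude this, and the pattern-mixture analysis explores it without removing it. Observing more SPIN scores reduces the problem at source.

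**Working it through.** **Inputs (Protocol, section 10).** Test level: "All the tests will be done at a 5% two-sided significance level". Power: "which will provide 90% power to detect a small between group effect size". Target: "effect size of Cohen's d=0.2 at 5% two-sided significant level". Allocation: "eligible participants will be randomized in a 1:1 ratio with no stratification". Attrition allowance: up to 50%. Planned total: 2104, or 1052 per group.

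**1. The plan's own figure.** n per arm = 2 × (1.960 + 1.282)² / 0.2² = 525.5, rounded up to 526. Allowing for 50% loss, 526 / (1 − 0.5) = 1052 per arm, or 2104 in total. This matches the Sample size section exactly, so the plan keeps 90% power at the loss it allows for.

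**2. Power at other levels of loss.** Power = Φ(0.2 × √(n/2) − 1.960), with n = 1052 × (1 − loss). Recovering a share r of non-responders turns a loss L into L × (1 − r). The documents give no response rate by type of reminder or length of questionnaire, so r is an assumption.

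| Loss before | Assumed r | Loss after | Observed per arm | Power |
|---|---|---|---|---|
| 50% | 0 | 50% | 526 | 0.900 |
| 50% | 10% | 45% | 579 | 0.925 |
| 50% | 20% | 40% | 631 | 0.944 |
| 50% | 30% | 35% | 684 | 0.959 |
| 60% | 0 | 60% | 421 | 0.827 |
| 60% | 10% | 54% | 484 | 0.875 |
| 60% | 20% | 48% | 547 | 0.911 |
| 70% | 0 | 70% | 316 | 0.710 |
| 70% | 10% | 63% | 389 | 0.797 |
| 70% | 20% | 56% | 463 | 0.861 |

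At 50% loss, 2104 × 0.5 = 1052 SPIN scores are missing at a time point. Recovering 10%, 20% or 30% of them adds about 105, 210 or 316 scores.

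**3. Bias, as an illustration.** In a complete-case comparison at one time point, bias = missing fraction × between-arm difference in the non-responder/responder gap. Assume that difference is 0.2 SD. At 50% loss the bias is 0.5 × 0.2 = 0.10 SD, half the target effect. At 45%, 40% or 35% loss it is 0.09, 0.08 or 0.07 SD, but only if the people recovered resemble those still missing.

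Steps 2 and 3 describe a two-group comparison at one visit. The planned model uses baseline SPIN and four follow-ups, so the figures show direction and rough size only.

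**The case against.** The strongest reply is that nothing here is wrong on the page. Texts are in use: one after randomisation, one near week 6 and one with each of four follow-up notices, six in all, in both arms. Neither statement about texts promises that later chasers will be texts. A reader might infer that the protocol contradicts itself; it does not, and this stands.

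A reader might also infer that chasers demand the whole battery and that anyone unwilling to complete it is lost for SPIN. That would be reading silence as a rule. The protocol does not say partial returns are refused, and its Statistical methods section lists item non-response separately from loss to follow-up. All that can be said is that no SPIN-only step is described.

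Nor can it be said that recoverable scores are being lost. The recovery rates and the 0.2 SD difference are assumptions, and recovered people may be the easier ones to reach, so bias need not fall in proportion.

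Finally, a short form could cost SF-36 and service-use data, which supply the QALYs and costs of the economic evaluation. That risk is real. It is small if the short link comes only as the last, unannounced chaser, since people who reach that stage would probably otherwise return nothing. Someone who has received it once could still wait for it at a later visit.

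**Conclusion.** The point holds as a weakness in a procedure that the protocol fixes: chasing after the first notice is by email only, with no stated fallback for the primary outcome, in a trial that expects to lose up to half its participants and holds mobile numbers with consent for texts. It is neither a contradiction nor a calculation error.

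A reader might infer from the 50% figure that the trial is underpowered. It is not, because the allowance is already in the 1052 per arm. The gain lies in less dependence on missing at random, and in cover beyond the allowance, where the plan has no margin: power is 0.868 at 55% loss, 0.827 at 60% and 0.710 at 70%. Under the assumed 10% to 30% recovery from 50% loss, power would rise from 0.90 to between 0.925 and 0.96. This is a worthwhile, cheap improvement whose actual yield the documents cannot establish.

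**What to change.** In the Follow-up measures section, identically for both arms:

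- send at least one of the three chasers as a text message;
- make only the final chaser, without announcing it beforehand, a link to SPIN plus the safety question;
- state that SPIN is saved when it is submitted.

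The cost is portal configuration and, if one chaser becomes a text, at most one automated text per non-completer per visit, to numbers already held and covered by consent. The downside is that SPIN-only responders will lack SF-36 and service-use data at that visit. The economic evaluation should count them separately from people missing everything, so that any drift towards the short form over the four visits can be seen.

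### Safety events may be counted by attribution to the intervention and then compared with a waiting list that has nothing to attribute them to; the protocol also does not say what a distressed participant is withdrawn from

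*Protocol*

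**What the plan says.** All references are to section 10 of the protocol.

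- **Follow-up measures, general statement.** "We will also record any safety (adverse) events (captured through monitoring participant feedback, and through questions at each follow-up period"). Nothing restricts this to one arm or to events with a particular cause.
- **Follow-up measures, what monitoring looks for.** Feedback is assessed, "including routine questions asked at each follow-up period as well as ad hoc correspondence such as emails or telephone calls", and the purpose given is "to see if these report an issue such as distress or anxiety caused by the intervention".
- **Follow-up measures, review.** "any possible adverse event will be reviewed by the study team (trial manager in discussion with lead investigator"). Events that are then classified as adverse go to the Trial Steering Committee, which has an independent chair and also acts as Data Monitoring Committee. No criterion for the classification is given, and masking of the first review is not stated.
- **Follow-up measures, action.** The example is "immediate action taken (such as withdrawing a participant who reports distress"). It does not say whether this means from the website, from the trial or from data collection.
- **Secondary outcome measures.** The list ends with "quality of life (SF-36); and safety events".
- **Statistical methods.** "Safety data will be analysed using Fisher’s exact or Chi-squared tests". The primary analysis is by intention to treat, using a mixed model valid under missing at random.
- **Control group; Initial trial flow.** Controls get nothing during the trial and are given the tool after the 12-month follow-up.

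**The concern.** A between-arm test of harm is valid only if an event has the same chance of being noticed and counted in each arm when the underlying risk is the same. The general statement meets that condition, but the worked description does not: a person on a waiting list cannot report distress caused by something not yet received. The study team's classification stands between a report and a counted event, and causation by the intervention is the only guide it is given.

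If attribution drives the count, the comparison sets attributed events in one arm against few or none in the other. It could then show harm where there is none. It also could not answer the useful question, which is whether people get worse more or less often with the tool than without it. In its account of the Cochrane review (section 9), the protocol names systematic attention to safety as a gap this trial will fill.

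The withdrawal wording is a smaller matter. If a participant is taken out of follow-up because of reported distress, the later scores are missing for a reason linked to the outcome.

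**Working it through.** **1. The plan's own figure.** The protocol gives no figure for safety events, so the only one to reproduce is the sample size. For d = 0.2, 90% power and two-sided 5%: n = 2 × (1.960 + 1.282)² / 0.2² = 525.4, so 526 per arm. With 50% attrition, 526 / 0.5 = 1052 per arm and 2104 in total. This matches the Sample size paragraph and is not affected by the point. It supplies the two arm sizes used below: 1052 randomised and 526 followed up.

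**2. Effect of asymmetric counting.** Let the true event rate be p in both arms, count every event in the intervention arm, and count only a share c of events in the control arm. Expected counts are N × p and N × p × c. For example, with N = 1052, p = 2% and c = 0.5, they are 21.0 and 10.5. The values of p and c are assumptions. The table shows how often Fisher's exact test rejects at two-sided 5% in 4000 simulated trials, although the true rates are equal.

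| N per arm | p | c = 1 (symmetric) | c = 0.5 | c = 0 |
|---|---|---|---|---|
| 1052 | 1% | 2.5% | 20% | 95% |
| 1052 | 2% | 3.6% | 41% | 100% |
| 1052 | 5% | 3.9% | 84% | 100% |
| 526 | 1% | 2.1% | 7% | 42% |
| 526 | 2% | 2.4% | 19% | 95% |
| 526 | 5% | 3.2% | 52% | 100% |

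The c = 0 column can be checked directly. With no control events, 5 against 0 gives a two-sided p-value of about 2 × (1/2)⁵ = 0.0625, and 6 against 0 gives about 2 × (1/2)⁶ = 0.031. The test therefore rejects whenever the intervention arm has six or more events. At p = 1% the binomial probability of six or more is 0.951 for N = 1052 and 0.430 for N = 526, in line with the simulation.

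Only control events are lost in this set-up, so the expected difference always points to harm from E-Couch.

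**3. Effect of distress withdrawals on SPIN.** Suppose a fraction w of the intervention arm contributes no SPIN score, and that these people would have been δ worse than the rest, whose mean is m. The full-arm mean is (1 − w)m + w(m + δ) = m + wδ, while the observed mean is m. The shift in favour of E-Couch is therefore wδ.

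- δ = 1 SD and w = 1%, 2%, 3%: shift of 0.010, 0.020, 0.030 SD, or 5%, 10%, 15% of d = 0.2.
- Wider range, w = 1% to 5% and unseen scores 0.5 to 1.0 SD worse than missing at random implies: 0.005 to 0.05 SD, or 2.5% to 25% of d = 0.2.

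For scale, the standard error of d with 526 per arm is √(2/526) = 0.062, so a shift of 0.030 is about half a standard error. The calculation ignores SPIN scores given before withdrawal and assumes no such withdrawals among controls, so for a given w and δ it leans towards a larger shift.

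**The case against.** The strongest reply is that the protocol does not define an adverse event by attribution. The general statement covers any event, the follow-up questions are not limited to one arm, and the causal phrase is introduced as an example of what monitoring includes. This stands, and it is why the point concerns a risk left open by the wording and not a stated counting rule. The risk remains because the example is the only guide offered for the classification step, and no choice of test can recover control events that were never classified.

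A second reply is that worsening among controls is already measured: SPIN, CES-D and the other scales are collected in both arms at every follow-up, and the main ones are compared by mixed model. This is true of average change. It does not give the proportion who get worse, which is what a harm comparison needs.

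A third is that the analysis plan, which is not shown, may define events and the handling of data after withdrawal. That may be so, but the two statements in the protocol still need to agree.

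Two stronger readings are tempting, and the protocol supports neither.

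- **That the worst outcomes drop out of the intention-to-treat and safety analyses.** The reported event precedes the withdrawal and stays in the count. SPIN scores given earlier stay in the mixed model. Reasons for withdrawal are shown by group, and pattern-mixture sensitivity analyses that do not assume missing at random are planned for the primary outcome.
- **That events are judged by people known to be unblinded.** The protocol does not state the masking of this review, and its design summary calls the trial double-blind. That label sits oddly with a waiting list, but it does not establish who knew what at this step.

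**Conclusion.** The point holds as an ambiguity with a real consequence for the safety comparison. The protocol's general promise and its only concrete description pull apart. If the description guides the counting, the Fisher or chi-squared result is not interpretable as a comparison of harm: at assumed equal rates of 1% to 5% with 1052 per arm, losing half the control events raises false rejection to between 20% and 84%. The direction would be against E-Couch, so this is not a route by which harm is hidden. How far counting would be asymmetric in practice cannot be known from the protocol.

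The withdrawal point is secondary. It depends on withdrawal meaning the end of follow-up, which the text does not say. Even then the shift in the SPIN result is probably a few hundredths of an SD, on assumed rates and assumed severity. The primary analysis is not in serious question.

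**What to change.** 1. **Counting.** Reconcile the two statements under Follow-up measures, so that the same adverse-event questions, worded without reference to cause, and the same counting rule apply in both arms. Make the between-arm harm comparison the proportion in each arm whose SPIN (and CES-D) worsens from baseline by a prespecified reliable-change amount at each follow-up. Report events attributed to the intervention descriptively, for the intervention arm only.
2. **Withdrawal.** Reconcile the withdrawal example with the intention-to-treat aim under Statistical methods. State that, whatever is decided about a participant's access to the site, follow-up questionnaires continue and the data stay in the analyses unless the participant withdraws consent to data collection. This leaves the clinical decision itself untouched.

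**Cost.** Changes of wording in the protocol and analysis plan, and one extra derived variable from scales already collected in both arms at every follow-up. No new assessment is needed. The drawback is that the worsening proportion can be calculated only for participants with follow-up scores, so it is exposed to the same attrition (planned for at up to 50%) as the other outcomes and should be reported with that caveat.

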Mediation analyses will be undertaken to determine if there is a dose-response effect of the intervention with more interaction with the website equating to higher levels of treatment effect (examining ‘dose’ in terms of number of total usage of site and numbers of modules completed). For both groups, their usage of the intervention will be recorded (total number of logins to site, total time on site, total number of modules completed). These will be tallied so that the total at 6 weeks, 3, 6 and 12 months can be computed and used in the analysis. We will also undertake mediation analyses to explore the effect of receiving other help for sub-clinical social anxiety symptoms during the trial on the treatment effect observed. If the program is effective those randomised to the control condition may be more likely to seek additional help elsewhere – a potential source of confounding which has the potential to reduce the observed effect. In addition, we will use a mediation model (Emsley et al., 2010; Mackinnon et al., 2002) to assess the influence of adherence/compliance to treatment outcome.

Other prespecified analyses will explore factors influencing response and non-response, and influencing adherence to the intervention (in terms of numbers of modules completed) and attrition from the trial (i.e. loss to follow-up). Factors which we will examine will include gender, age, ethnicity, other sources of help/support, severity of symptoms, etc. Exploratory analyses of usage data will allow us to examine any dose response effect of the intervention, and to examine whether certain components of the intervention have more benefit than others.

We will explore the mechanism of missing data by looking for associations between participant characteristics and the likelihood of non-response to questionnaires at different time points. This can be done using a regression model for binary outcomes (1=response; 0=non-response) with independent variables measured at baseline (gender, age, educational attainment, marital status, baseline questionnaire scores (FNE, SPIN, CES-D, SWEMWBS, SF-36)). If significant associations are observed this lends weight to a missing at random (MAR) assumption. The primary outcome analysis will utilise a mixed effects model which implicitly accounts for data under a MAR assumption.

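### Both of the protocol's rules for judging missing at random are invalid, and the primary model's MAR protection does not extend to seven of the nine baseline variables listed as possible predictors of non-response

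*Protocol*

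**What the plan says.** All of this is in Protocol section 10, under Statistical methods and Sample size.

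- **Primary model.** A mixed effects model for SPIN at 6 weeks, 3, 6 and 12 months with a time-by-group interaction. On covariates: "The model will adjust for the SPIN score at baseline gender". A word is evidently lost. I read it as baseline SPIN and gender.
- **Missingness check.** Response (yes/no) is regressed on nine baseline variables: gender, age, education, marital status, FNE, SPIN, CES-D, SWEMWBS and SF-36. The reading to be given to it is: "If significant associations are observed this lends weight to a missing at random (MAR) assumption".
- **Claim for the primary model.** "The primary outcome analysis will utilise a mixed effects model which implicitly accounts for data under a MAR assumption".
- **Sensitivity analysis.** Methods that do not assume MAR, such as pattern-mixture models. If they give different results from the mixed model, "it is likely that the MAR assumption is not valid".
- **Scale of the problem.** "we intend to recruit 2104 participants (i.e. 1052 per group) to this trial", for "90% power to detect a small between group effect size of Cohen's d=0.2 at 5% two-sided significant level", with up to 50% attrition allowed for.

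The protocol does not say that a baseline variable found to predict non-response will enter the primary model.

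**The concern.** The two interpretive sentences give readers of the trial report the wrong guide to its largest threat.

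The first turns a warning into reassurance. A dropout regression with significant terms would be reported as support for the primary analysis, although MNAR dropout produces the same finding. The second treats the sensitivity analysis as a test of MAR. The observed data cannot provide such a test, because the answer depends on what is assumed about unobserved scores.

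The third issue is the gap between the variables suspected of driving dropout and those the model conditions on. Likelihood-based validity under MAR is not a general property of mixed models. It holds for missingness that depends on the arm, the covariates and the observed outcomes in that model. If dropout depends on, say, baseline CES-D, the data may be MAR given everything collected but not MAR given what is modelled.

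With half the outcomes possibly missing and an effect of 0.2 SD sought, a modest bias is large relative to both the effect and its standard error.

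**Working it through.** **1. The plan's own figure.** n per arm = 2(1.960 + 1.282)²/0.2² ≈ 525.5, so 526. Dividing by 1 − 0.5 gives 1052 per arm and 2104 in total, with power 90.0%. The stated size reproduces. With 526 analysed per arm, the unadjusted standard error is √(2/526) = 0.062 SD.

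**2. Covariate count.** Of the nine listed variables, two (SPIN, gender) are in the model. Seven are not: age, education, marital status, FNE, CES-D, SWEMWBS and SF-36.

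**3. Simulation.** From the protocol: N = 2104, 1:1 allocation, four visits, effect −0.20. The rest is assumed, since the documents give no correlations or dropout slopes:

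- Standardised baseline SPIN and CES-D with correlation 0.5.
- Outcome = 0.4·SPIN + 0.3·CES-D + 0.1·gender − 0.2·arm + 0.55·(person effect) + 0.5·(noise), with within-arm SD about 0.96.
- Monotone dropout reaching 47–48% by 12 months.
- 500 replicates; Monte Carlo SE 0.002.

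The fitted model is maximum likelihood with unstructured covariance, adjusting for SPIN and gender, then again with CES-D added. The association check regresses 12-month response on gender, SPIN and CES-D.

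| Dropout depends on (log-odds per SD) | Association check significant | SPIN + gender model | CES-D added |
|---|---|---|---|
| Unobserved current SPIN, ±0.6 in opposite directions by arm, plus CES-D 0.4 (MNAR) | 100% | −0.38 | −0.36 |
| Baseline SPIN, 0.6 in both arms (MAR given the model) | 100% | −0.20 | −0.20 |
| CES-D, 0.6 in both arms | 100% | −0.20 | −0.20 |
| CES-D, 0.2 control, 0.6 intervention | 100% | −0.23 | −0.20 |
| CES-D, −0.6 control, +0.6 intervention | 15% | −0.29 | −0.20 |
| CES-D, 0.6 in both arms, and CES-D modifies the effect by 0.15 per SD | 100% | −0.17 | −0.17 |

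**4. The first rule.** The check is significant in every replicate in rows 1 and 2. In row 2 the estimate is right; in row 1 it is off by 0.38 − 0.20 = 0.18 SD. The check does not distinguish them. In row 5, where omitting CES-D does most harm, it is significant in only 15% of replicates. That is about the chance rate for three tests at 5% (1 − 0.95³ = 14%), because opposite slopes cancel when the arms are pooled.

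**5. The second rule.** In row 2, MAR holds and the mixed model is unbiased. A pattern-mixture analysis that shifts intervention-arm dropouts by 0.2 SD gives −0.20 + 0.2 × 0.478 ≈ −0.10. The results differ, so the rule would call a true MAR assumption unlikely. The whole difference is the chosen shift times the dropout proportion.

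**6. The omitted variables.** Bias is 0 in row 3, 0.03 in row 4 and 0.09 in row 5. The last two are 15% and 47% of d=0.2, or about 0.5 and 1.5 standard errors (0.030/0.062 and 0.094/0.062). Adding CES-D removes both. In row 6 the bias is 0.03 and a main effect of CES-D does not remove it; that case needs terms that differ by arm.

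**The case against.** **Neither sentence is a decision rule.** The mixed model is fitted whatever the association check shows, and the pattern-mixture analysis is run in any case. No estimate or test changes, and the second error is cautious, since it leads the authors to doubt MAR. This stands and limits the severity. It does not make either inference correct, and no detail in an unseen SAP could.

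**A non-MAR sensitivity analysis is already planned.** True, and that is the right general remedy. The fault is the reading attached to it.

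**Covariates and auxiliary variables are SAP matter, and the covariate sentence is garbled.** This partly stands. The SAP may add variables, so their absence is not by itself counted as an error. What the protocol does state is a MAR claim that is not tied to the model's contents, beside a list of suspected predictors that are mostly outside it.

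**The sizes depend on assumptions.** This stands. An omitted scale that overlaps heavily with baseline SPIN, as FNE may, adds little given SPIN, and the bias shrinks accordingly. The MNAR bias in row 1 would affect any MAR analysis, including one with more covariates (−0.36), so it is not a cost of the short covariate list.

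**A stronger reading.** A reader might infer that the model's MAR claim fails even when MAR is true, or that the primary estimate is biased. The documents do not support that. The omitted variable must predict SPIN given the model, and its link to dropout must differ by arm or it must modify the effect. Otherwise the contrast was unbiased. Nor is it an error that participants with no follow-up SPIN drop out of the likelihood; this is valid under MAR given the covariates.

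**Conclusion.** The two inferences are wrong as written. Associations between baseline variables and non-response are evidence against MCAR only. A differing pattern-mixture result shows sensitivity to the assumption imposed, not that MAR is likely false.

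The covariate gap is a conditional weakness. Seven of nine listed variables lie outside the model, and the possible bias in the treatment contrast ranges from none (equal slopes, no effect modification) to 0.03–0.09 SD (slopes differing by arm), under assumed slopes and correlations. A waiting-list design makes different dropout behaviour by arm plausible, but the documents give no data on it. Confidence is high on the two inferences and lower on the size of any bias. Severity: should-fix.

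**What to change.** 1. Delete the sentence that associations support MAR, or restate it as evidence against MCAR only. If the regression is kept, include arm and arm-by-baseline terms, since a pooled model can miss the pattern that matters.
2. Replace the different-results rule with a pattern-mixture sensitivity analysis over a prespecified range of shifts in unobserved SPIN, applied separately by arm. Report the shift at which the conclusion changes, and do not present it as a test of MAR.
3. Tie the MAR statement to the variables in the model. Include the listed baseline predictors as covariates in the mixed model, or as auxiliary variables in an imputation-based supporting analysis. Imputing separately by arm would also allow for effect modification, which main-effect adjustment does not.

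The cost is a somewhat larger model and modest extra analysis. The variables are already collected at baseline, and multiple imputation is already planned for the economic evaluation. That evaluation says it will explore missing data with the same strategies, so the corrected wording should carry over to it.
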